### Process evaluation

Since our project contains multiple components, the process evaluation during and after the trial is guided by the framework for the design and evaluation of complex interventions [22,23]. Utilizing a combination of qualitative and quantitative methods, process evaluation for the complex interventions in our cRCT can explore the mechanism of achieving the intervention effects [24]. In other words, we can get insights into a series of questions such as ‘What interventions are effective in which policies and implementation environments, for whom and why?’ We will conduct around 30 in-depth semi-structured interviews with leading personnel at all levels of health agencies, township and village doctors, county hospital staffs, social workers, and trial participants in the intervention group.

Our specific objectives for the process evaluation include: 1) to determine intervention accessibility by the number of subjects receiving screening, presented to county hospitals, and under treatment, as well as their feedbacks; 2) to explore the intervention effectiveness (reasons for both effectiveness and ineffectiveness), along with the relationship between interventions and expected results; 3) to access the acceptance of intervention implementation at the organization level and the staff level – any conflicts with existing management or policies, and corresponding adjustment; 4) to report intervention fidelity, the degree and quality of intervention completion, as well as challenges and unexpected results, at both subcluster-level and individual level.

#### Analysis of process evaluation.

All the recorded interviews will be transcribed and translated into English before qualitative analysis. We will use NVivo 10 software to process and analyze our qualitative data guided by a framework analysis as described by Gale at al [25], to identify themes related to our process evaluation objectives. The findings will be reported based on the Consolidated Criteria for Reporting Qualitative Research (COREQ) guidelines [26].

### Costing study

This study will measure the incremental cost-effectiveness of interventions compared with conventional TB finding, using research data and literature to evaluate both health system and social benefits. We will compare costs and outcomes of the intervention group to those of the control group throughout the 24-month trial. The objective of the costing study is to calculate the incremental cost-effectiveness ratio (the increased costs required for each 1% reduction in the prevalence of active TB among high-risk populations) using data from the project’s primary outcome.

#### Data collection.

We will send out a questionnaire to directors of all recruited township or village hospitals to collect health care resources used in the trial, along with their costs. The data include: 1) average salaries, in Renminbi (RMB), for each level of staff in designed hospitals who participated in this project and their estimate of time working on the project; 2) average salaries, in RMB, for township and village doctors who do not work in designated hospitals but still participated in the project and their estimate of time working on the project; 3) average salaries, in RMB, for social workers and other personnel worked in the project implementation and their estimate of time working on the project; 4) cost for TB screening (i.e., symptom screening, chest DR, mobile van operation, sending samples to county hospitals) and laboratory test (e.g., sputum smear, culture, and GeneXpert); and 5) indirect costs of ACF participants (loss of earnings due to participating in the screening, in RMB). To optimize the data quality, we will double-entry and random-check the input data.

#### Estimation of resources use and costs.

Healthcare resources in this case include resources used for TB detection and diagnosis. The cost per patient is calculated as the sum of consultation, screening and laboratory testing. The total costs is calculated for the main analysis population as described in the Statistical Analysis section [27].

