### Study design and setting

We will conduct a parallel two-group, cluster randomized controlled trial of a comprehensive package of active case finding followed by timely treatment in rural Guangxi China to evaluate whether the interventions could reduce the TB epidemic compared to the usual care (Fig 2). Guangxi is located in southwest China, bordering with Vietnam. Guangxi reported 31,913 TB cases with a notification rate of 70/100,000 in 2020 among all populations, representing the second highest TB burden in China. Of the reported TB cases, 74% were from rural areas, and 30% were elderly ( ≥ 65 years old). Mountainous areas in Guangxi had high TB notification rates; for example, the two trial counties (Xincheng and Xiangzhou of Laibin Prefecture) reported an average notification rate of 134/100,000, which is two times the provincial average. In addition, the Covid-19 pandemic has substantially delayed TB diagnosis and treatment, which would fuel up TB transmission and exacerbate the TB epidemic.

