We will also collect costs from patient, health system and societal perspectives to conduct an incremental costing study. We will collect process indicators that include a) the proportion of bacteriologically confirmed cases identified by active case finding in the intervention group; b) the yield rate of our intervention, which is the number of bacteriologically confirmed cases per 100 persons screened using each strategy.

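### The ICER credits the intervention with a fall in TB prevalence that depends on treatment, but its costs stop at diagnosis, which does not match the perspectives the protocol names

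*Protocol article*

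**What the plan says.** The protocol article describes the intervention under Study design and setting as "a comprehensive package of active case finding followed by timely treatment". Under Outcomes it states: "We will also collect costs from patient, health system and societal perspectives to conduct an incremental costing study".

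The Costing study section sets the comparison: "This study will measure the incremental cost-effectiveness of interventions compared with conventional TB finding". It defines the ratio as "the increased costs required for each 1% reduction in the prevalence of active TB among high-risk populations" and adds: "We will compare costs and outcomes of the intervention group to those of the control group throughout the 24-month trial".

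Estimation of resources use and costs then fixes what is counted. "Healthcare resources in this case include resources used for TB detection and diagnosis", and "The cost per patient is calculated as the sum of consultation, screening and laboratory testing".

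The costing Data collection section lists staff salaries and project time, screening and laboratory costs, and earnings that participants lose by attending screening. Estimation of implementation costs lists training, materials, van, driver, AI set-up, questionnaires and sample transport, and keeps all of these outside the cost-effectiveness analysis.

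**The concern.** The two halves of the ratio cover different things. The effect is measured in Year 3, after patients found in Year 1 have been treated; the protocol inserts a waiting year for that purpose. The cost ends when a diagnosis is made. Treating additional patients is part of what produces the effect, and under the stated perspectives someone pays for it.

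At stake is the meaning of the ICER. As specified, it is the detection and diagnosis cost per unit of prevalence reduction. A reader deciding on scale-up could take it for the cost to the health system or to society of achieving that reduction, and it is neither. The primary outcome, the design and the power are unaffected.

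**Working it through.** The article gives no unit cost and no ICER, so there is no figure to reproduce. The check is mainly textual.

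**1. The effect passes through treatment.** The ratio is per 1% reduction in prevalence, not per case found (Costing study). Under Research activities apply to both groups, the trial waits a year so that Year 1 patients can finish treatment. Under Intervention, both bacteriologically and clinically confirmed patients are referred for treatment.

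**2. Treatment is a cost under the named perspectives.** Study design and setting says that drug-susceptible disease is treated under a public free-treatment policy and that insurance covers drug-resistant disease. It also describes monthly County Hospital visits and village-doctor support. These use health-system resources and patients' time.

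**3. The amount of treatment should differ between arms.** The Introduction argues that active case finding reaches patients whom passive finding delays or misses. The regimen per patient may be the same in both arms, but the number of patients treated is not expected to be.

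**4. No section supplies the missing term.** The cost sum has three components, none of them treatment. The data list has no entry for drugs, treatment visits, treatment support or patient costs during treatment. The implementation list has none either, and is excluded from the ratio anyway.

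**5. Illustration of scale.** From the document: 255 villages, 12 of 23 townships in the intervention arm, about 500 eligible people per village, prevalence 300 per 100,000. Assuming townships of average size:

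- Eligible people in the intervention arm: 255 × 12/23 × 500 ≈ 66,500.
- Prevalent confirmed cases: 66,500 × 0.003 ≈ 200.
- Cases found, assuming 50–100% coverage and 70–90% detection: 200 × 0.5 × 0.7 ≈ 70 to 200 × 1.0 × 0.9 ≈ 180.

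Let R be the treatment cost per case divided by the finding cost per person screened. Let f be the net extra treated cases as a share of prevalent cases. Both are assumed. Treatment then adds 0.003 × f × R to incremental cost, taken relative to the finding cost:

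| f | R = 50 | R = 100 | R = 500 |
|---|---|---|---|
| 0.25 | 3.75% | 7.5% | 37.5% |
| 0.5 | 7.5% | 15% | 75% |
| 1 | 15% | 30% | 150% |

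For example, 0.003 × 0.5 × 100 = 0.15. Clinically diagnosed patients would raise f. Patients whom usual care would have treated in the same window lower it, as do cases averted. If averted cases outnumbered the extra cases found, f would be negative.

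**The case against.** The strongest reply is that the protocol openly declares a case-finding costing. Its comparator is conventional TB finding, its resource definition says detection and diagnosis, and diagnosed patients in both arms receive the same routine treatment. Perspective concerns whose costs count, whereas scope concerns which activities are costed. Each perspective is partly represented, since staff time and participants' lost earnings are both collected.

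Some of this stands. The protocol names three perspectives, so calling the analysis simply societal would be wrong, and the patient side is not empty. But a finding-only scope would suit a ratio per case detected, and this one is per 1% of prevalence. Identical treatment per patient does not cancel when the arms treat different numbers. The only patient-side item is also confined to attending screening.

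A second reply is that the method is only partly visible. The Costing study section mentions research data and literature for evaluating benefits, and the approved proposal is in a supplement not shown. This matters for savings. A reader might infer that savings from averted cases are excluded too, but no section rules them out. It does not put treatment into the stated sum; the word for inclusion might be read as open-ended, but the sentence that follows gives the components.

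A reader might also infer that the protocol promises policy makers a societal ICER. It does not: the sentence about policy makers concerns the separate implementation-cost estimate, and the ICER carries no perspective label.

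**Conclusion.** The mismatch holds. Followed as written, the plan gives a ratio that omits a publicly funded or insured cost of producing its own effect, and this does not fit the perspectives named under Outcomes. That conclusion is textual and needs no cost assumption.

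Its size is unknown. The table spans 3.75% to 150% under assumed values, so the omission may be minor or material. A reader might go further and conclude that the ICER is understated by a known amount, for instance by charging a full course to each of the roughly 200 prevalent cases. The document does not support that. Such a figure is gross: it ignores incomplete detection, patients whom usual care would treat anyway and cases averted, and every unit cost in it would be assumed. Even the sign of the net effect is not fixed.

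This should be corrected before the costing analysis is run. It concerns an ancillary analysis only.

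**What to change.** Either of two changes resolves it.

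**Preferred: add treatment costs to the ICER in both arms.** Count patients diagnosed and registered within the 24-month costing window and multiply by a unit cost per treatment course. Laboratory testing and clinical consultation already provides for collecting National TB Program cases in both groups over three years. Three details need stating:

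- Say which 24 months are meant, because Study status and timeline gives 36 months for the main trial.
- Exclude cases detected only by the Year 3 prevalence survey. The survey is a research activity in both arms, and all diagnoses enter the registry. If the intervention works, the survey finds more cases in control townships, and costing them would charge that arm for treatment that usual care would not have generated.
- Estimate drug-resistant treatment and patient-side treatment costs from insurance data or literature, and vary them in a sensitivity analysis. A program unit cost alone would miss both.

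**Alternative: relabel.** Call the result a case-finding (detection and diagnosis) cost ratio, and drop the health-system and societal perspectives for it.

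The first option takes some extra unit-cost work, since the article names no source for treatment costs and does not say whether regimen type is recorded. The ratio may become less favourable. The second option needs only a change of wording, but leaves decision makers without the cost of obtaining the prevalence reduction.

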#### Estimation of implementation costs.

The implementation costs are calculated separately and will not be accounted in the cost-effectiveness analysis. The objective of this estimation is to inform policy makers and stakeholder of the potential cost to facilitate their decision on whether to implement the intervention at scale. For each cluster, the implementation costs included the cost of training for personnel, the cost of personnel to attend training, the costs for developing and printing the handbook or guidelines per training attendee, operation cost of mobile van, driver cost, setup cost of AI facilitated DR, the costs for producing symptom questionnaires used in the project, and the costs of sending samples back to county hospitals.

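### The cost-effectiveness ratio has a contradictory cost set: van operation and sample transport are both counted and excluded, and its effect measure is not fixed

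*Protocol article*

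**What the plan says.** All references are to the protocol article.

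- **Costing study (opening paragraph).** The comparison is stated as "This study will measure the incremental cost-effectiveness of interventions compared with conventional TB finding". The ICER is defined as "the increased costs required for each 1% reduction in the prevalence of active TB among high-risk populations", calculated with data from the primary outcome.
- **Data collection (costing study), item 4.** Screening cost is defined as "cost for TB screening (i.e., symptom screening, chest DR, mobile van operation, sending samples to county hospitals". Laboratory tests follow in the same item.
- **Estimation of resources use and costs.** "Healthcare resources in this case include resources used for TB detection and diagnosis", and "The cost per patient is calculated as the sum of consultation, screening and laboratory testing".
- **Estimation of implementation costs.** "The implementation costs are calculated separately and will not be accounted in the cost-effectiveness analysis". The items classed this way include training, handbooks, questionnaires, "operation cost of mobile van, driver cost, setup cost of AI facilitated DR" and "the costs of sending samples back to county hospitals".
- **Outcomes.** The primary outcome is prevalence of bacteriologically confirmed TB in Year 3. Prevalence of active TB, which adds clinically confirmed cases, is the first secondary outcome.

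**The concern.** Two cost items stand on both sides of the line that decides what enters the ICER. Two analysts following the article in good faith could produce different ratios from the same data.

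The stricter rule also removes costs that belong to the intervention. Under the Intervention heading, the package is delivered by driving a van with AI-aided radiography to villages and carrying sputum to the county hospital daily. Under Usual care, control townships receive no active case finding. The costs of van, driver, AI set-up and transport therefore arise in one arm only, and leaving them out makes the intervention look cheaper per unit of effect than it is.

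The effect side has a separate problem. The ratio is worded for active TB but sourced from the primary outcome, which is a different quantity, and the scale of a 1% reduction is left open.

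The costing study is meant to inform scale-up, and the ICER is its headline figure. The primary effectiveness comparison is not affected.

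**Working it through.** The article states no ICER, unit cost or cost total, so there is no figure to reproduce. The check is an item-by-item comparison, a direction argument, and an illustration under stated assumptions.

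**1. Cost lists side by side**

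| Item | Data collection, item 4 (counted through the cost per patient) | Estimation of implementation costs (excluded) | Status |
|---|---|---|---|
| Van operation | yes | yes | contradictory |
| Sample transport to county hospital | yes | yes | contradictory |
| Driver | not named | yes | excluded |
| Set-up of AI radiography | not named | yes | excluded |
| Chest radiography itself | yes | no | counted |
| Symptom screening | yes | only production of the questionnaires | counted, apart from materials |
| Smear, culture, GeneXpert | yes, as laboratory tests | no | counted |
| Training, handbooks | not named | yes | excluded |

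**2. Direction**

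Let C_I and C_U be the costs of the intervention and usual-care arms, and E the reduction in prevalence.

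- Full ICER = (C_I − C_U) / E.
- The excluded delivery items occur in C_I only. If they make up a share f of the full increment, then reported ICER = (1 − f) × full ICER, so full ICER = reported ICER / (1 − f).
- With E > 0 and f > 0, the reported ICER is too low.

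What f contains depends on which section governs:

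- Implementation-cost rule governs: van operation, driver, sample transport, AI set-up, training and materials.
- Screening-cost list governs: driver, AI set-up, training and materials only.

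The direction is the same in both cases; the second gap is smaller.

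**3. Illustration (f is assumed, since the document gives no basis for it)**

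| Assumed f | Reported / full = 1 − f | Full / reported = 1 / (1 − f) |
|---|---|---|
| 10% | 0.90 | 1.11 |
| 30% | 0.70 | 1.43 |
| 50% | 0.50 | 2.00 |

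**4. Effect measure**

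The Sample size section plans for 300 per 100,000 falling to 150 per 100,000, for bacteriologically confirmed TB.

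- Baseline: 300 / 100,000 = 0.30%.
- Planned absolute reduction: 0.30% − 0.15% = 0.15 percentage points.
- Planned relative reduction: 0.15 / 0.30 = 50%.

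Read as percentage points, one unit of the ICER (1 point) exceeds the whole assumed baseline of about 0.3%. Read as relative percent, the planned effect is 50 units. The corresponding figures for active TB are not given.

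**The case against.** The strongest defence is that the exclusion is open and deliberate. The article says that implementation costs will be estimated separately so that policy makers can weigh them when deciding on scale-up, so nothing is hidden from that decision. Reporting one-off items such as training and handbooks apart from the ICER is a defensible convention, and this part of the defence stands. It does not carry over to van operation, driver and transport, which recur with the village visits and the daily sample runs.

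A second defence is that item 4 under Data collection is only a list of what to collect, so the implementation-cost section governs and nothing conflicts. But the resource-use section puts screening into the cost per patient, and item 4 is the only place in the costing study that says what screening cost consists of. Even if this defence succeeds, the outcome is the larger omission.

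Third, a reader might infer that all four delivery items are listed elsewhere as screening costs. They are not: that holds for van operation and sample transport only. Driver cost and AI set-up are named only as implementation costs, and item 3 under Data collection, which covers pay and time of other project personnel, might take in drivers. Nor is all AI radiography excluded, since chest radiography remains a screening cost.

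Fourth, the relative reading of a 1% reduction is the natural one, because the Sample size and Discussion sections both express the expected effect as a relative 50%. That is fair. A reader might take the gap between the two scales (50 / 0.15, about 333-fold) for a bias; it is a change of units, and a clarifying word removes it.

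**Conclusion.** The point holds as a contradiction in the cost set together with a conditional downward bias. Van operation and sample transport are both counted and excluded. If the implementation-cost rule is followed, the ICER omits core delivery costs and is too low, provided the intervention lowers prevalence. If the screening-cost list is followed, the omission shrinks to driver, AI set-up, training and materials.

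The size is unknown. The factor of 1.11 to 2.00 rests wholly on the assumed excluded share of 10% to 50%. A reader might infer that most of the incremental delivery cost is left out, or that understatement is certain under every reading and by a known amount. The document supports neither, because it gives no cost for any item and the governing section is unclear.

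On the effect side, the defect is a mismatch between the outcome named and the data source, plus an unstated scale. A reader might conclude that the denominator is no defined outcome at all; active TB prevalence in high-risk populations is in fact the first secondary outcome.

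This should be corrected before the costing analysis.

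**What to change.** 1. Assign each cost item to one category and count it once. Reconcile the costing study's opening paragraph, Data collection, Estimation of resources use and costs, and Estimation of implementation costs.
2. Include van operation, driver, sample transport and the annualised set-up cost of AI radiography in the intervention-arm cost of the base-case ICER.
3. Report training and materials separately, or add them in a sensitivity analysis.
4. Name one effect measure and its scale, for example relative percent reduction in bacteriologically confirmed prevalence, with active TB as a secondary ratio.

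The cost is a change of wording in the costing plan, since the article already plans to estimate every one of these items. The downside is a less favourable ICER.

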### Trial management

Guangxi CDC will lead this project and have full access to all the anonymized data and information associated with the trial. We will establish a data monitoring committee (DMC) to ensure all data are collected in conformity with the agreed ethical guidelines, stored in Guangxi CDC properly and used for research purposes only. Meanwhile, the DMC is also responsible for the safety and privacy protection of all the subjects and providers participated in the trial. Additionally, there will be a trial steering committee (TSC) lead by external members to generate the progress of the trial. We will hold regular online meetings with both DMC and TSC every 6 months to get updates and discuss any protocol modifications, starting from the beginning of the study, until it completes. If there are any changes or concerns needed to report or discuss, the committees can meet on an ad hoc basis with the co-leaders as well. Moreover, a trial management unit (TMU) will be established in consisting of three local staff. The responsibility of the TMU is to better manage the day-to-day activities of the trial according to the study protocol.

